## Abstract

**Background:**

Chronic neuropathic pain in thalamic pain syndrome remains intractable. Its poor response is ascribed to destruction of the integrated neuromatrix in experience of pain. Deep brain stimulation is a promising technique to modulate activity of implicated structures. However, traditional approaches targeting sensori-motor substrates have failed to affect disability. The offending lesion in thalamic pain syndrome that almost invariably destroys sensory pain pathways may render these classical approaches ineffective. Instead, we hypothesize that targeting structures representing emotion and affective behavior-ventral striatum/anterior limb of the internal capsule, may alleviate disability.

**Methods/design:**

We present the design of our phase I randomized, double-blinded, sham-controlled, crossover trial that examines safety, feasibility and efficacy of our proposed approach. In our ongoing trial, we intend to enroll ten patients with thalamic pain syndrome. Following implantation, patients are randomized to receive active deep brain stimulation to the ventral striatum/anterior limb of the internal capsule or sham for 3 months, after which they are crossed over. The primary endpoint is Pain Disability Index. Other outcomes include visual analog scale, depression and anxiety inventories, quality of life, and functional neuroimaging.

**Discussion:**

Designing trials of deep brain stimulation for pain is challenging owing to the ethical-scientific dilemma of introducing a control arm, complicated blinding, heterogeneous etiologies, patient expectations, and inadequate assessment of disability. The quality of evidence in the field is classified as level III (poor) because it mainly includes a multitude of uncontrolled case series reporting variable outcomes, with little regard for the placebo effect related to implantation. Without valid data on efficacy, use of deep brain stimulation for pain remains “off label”. We present our trial design to discuss feasibility of conducting sham-controlled phase I studies that may represent significant refinement for the field. Double-blinding would reduce influence of patient expectations and therapeutic confusion amongst investigators. With a cross-over approach, the dilemma regarding including a control group can be mitigated. Use of homogeneous etiology, measurement of disability, depression and quality of life, besides pain perception, all represent strategies to evaluate efficacy rigorously. Functional imaging would serve to define mechanisms underlying observed effects and may help optimize future targeting.

**Trial registration:**

Clinicaltrials.gov NCT01072656

## Background

### Thalamic pain syndrome: refractoriness to traditional management

Chronic neuropathic pain, defined as ‘pain initiated or caused by a primary lesion or dysfunction in the nervous system’ [1], is one of the most prevalent disorders, affecting about 8% of adults [2]. Although it can be associated with peripheral or central pathology, pain of central origin, such as that following stroke, is more resistant to treatment [3-5]. In fact, pain associated with lesions of somatosensory thalamic nuclei or somatosensory thalamo-cortical projections, following subcortical stroke, is particularly intractable and extraordinarily frustrating for patients and physicians. Also referred to as thalamic pain syndrome (TPS) or Dejerine-Roussy syndrome, the disorder is characterized by unrelenting pain, associated paradoxically with numbness (anesthesia dolorosa) on the affected side. Its prevalence is estimated to be 8% across all stroke patients but can be as high as 18% in those with sensory deficits [6].

Poor responsiveness in TPS is attributed to disruption of the pain neuromatrix [7]. The neuromatrix is an integrated framework of somatosensory, limbic and cognitive networks in the brain interacting with thalamo-cortical pathways in the experience of pain. Since mechanisms of pain in TPS span across such widespread cerebral structures within the neuromatrix, a promising technique involves modulating activity of these structures with invasive deep brain stimulation (DBS) [8].

Almost four decades ago [9] DBS was introduced to target structures involved in pain transmission and opioid-mediated analgesia, such as the periventricular and periaqueductal gray matter. Fifteen years later, results continued to be disappointing in TPS [4] even though response across other etiologies was staggering. Emphasis was then shifted to target the sensory thalamic nodes based on the premise that stimulating the thalamus would inhibit hyperactivity within pain-transmitting neuronal fibers associated with unrelenting pain in TPS [10]. DBS of the ventral posterior nuclei of the thalamus, however, generated inconsistent benefit [4,5]. More recently, motor cortex stimulation (MCS) was introduced as a less invasive alternative, based on the hypothesis that motor cortical influence via cortico-thalamic pathways would reduce thalamic hyperactivity in pain [11]. Tsubokawa *et al*. initially demonstrated positive results across several central pain syndromes [12], but promise for patients with TPS was subsequently irreproducible [13-16]. Thus, it is critical to re-evaluate substrates that have been targeted with DBS, to understand and resolve reasons for their failure in TPS over the last 40 years.

### Importance of identifying novel nodes for targeting with DBS in TPS

We suggest there may be several reasons for failure of traditional DBS that targets sensorimotor substrates in management of TPS. First, the offending lesion in TPS damages sensorimotor targets such as the ventral-posteromedial and ventral-posterolateral targets that are critical to conduct the effects of contemporary DBS [11,17]. Second, since pain experience and disability is an integrative phenomenon of nociception influenced by affect and cognition [7], substrates that are key for regulation of emotion and behavior, such as ventral striatum (VS) and anterior limb of the internal capsule (ALIC), could be more effective in influencing the experience of disability. Patients with TPS experience severe allodynia and suffer from learned behaviors of anticipating pain, which exacerbates disability. DBS that modulates VS/ALIC may modify learned affective behavioral responses [18] as in obsessive compulsive disorder [19] and depression [20] and, thus, would potentially be more effective in mitigating pain-related disability.

### Challenges in designing a clinical trial of DBS in treatment of TPS

Our group has recently suggested departing from the traditional approach of targeting DBS to sensorimotor substrates and instead provided rationale for a novel DBS target involving VS/ALIC in the management of chronic neuropathic pain in TPS [21]. Examining efficacy of a novel node of DBS in a population with refractory chronic neuropathic pain, however, is challenging because the paradox of experience-subjectivity of pain affects assessment of outcomes, while patient expectations from the investigational procedures as well as surgical and neuro-stimulation interventions may generate several confounds. The quality of contemporary evidence regarding effectiveness of DBS in pain is currently classified as level III because studies thus far, have enrolled heterogenous etiologies, incorporated inadequate experimental blinding and controlled poorly for confounds of placebo. In addition, little regard has been given to the risk for therapeutic confusion in the investigative team about benefits of treatment, or to key outcome measures that evaluate the experience/disability of pain or its effect on quality of life, rather than severity on a numerical scale of pain perception [8,22].

### Objectives and hypothesis

Here, we present the protocol design of our current pilot clinical trial where we examine: 1) safety and feasibility of delivering DBS to VS/ALIC in a double blinded, randomized, sham-controlled, crossover clinical trial in patients with TPS; 2) efficacy of the intervention with respect to pain-related disability, quality of life, neuropsychological and psychiatric outcomes and individual ratings of perception of pain; and 3) reorganization within affective networks of the pain neuromatrix with DBS delivered to VS/ALIC, which will be studied using functional magnetic resonance imaging (fMRI) and magneto-encephalography (MEG).

We hypothesize that DBS targeting VS/ALIC will modulate the affective component of TPS and consequently, improve pain-related disability.

## Methods

### Study design

A pilot, randomized, sham-controlled, double-blinded, two-group crossover clinical trial design is being employed to evaluate the safety and effectiveness of DBS targeting VS/ALIC in TPS. Patients with TPS are being enrolled, and then randomized to active DBS or sham following implantation, after which they are crossed over. The study has been approved by the Food and Drug Administration with an Investigational Device Exemption as a phase I clinical trial, and is registered (http://clinicaltrials.gov/ct2/show/NCT01072656) as a clinical trial. The Institutional Review Board of the Cleveland Clinic has approved the study. Informed consent is obtained from all interested participants in accordance with policies of the Board.

### Patient population and recruitment

We are actively enrolling for this study. We intend to enroll a total of 10 patients with TPS, such as that following stroke, surgical injury or focal traumatic injury, proven refractory to conventional pain management. The selection criteria are developed to enroll patients with intractable pain contralateral to a brain lesion, without severe psychiatric or cognitive comorbidities, suicide ideation, major uncontrolled medical problems or previous ablative surgery for TPS. Patients who have had motor cortex stimulation (MCS) but not DBS are also candidates, provided that the MCS hardware has been removed. Inclusion and exclusion criteria are discussed in detail below.

#### Inclusion criteria

•Age > 21 years

•Diagnosis of TPS >6 months

•MRI-confirmed lesion affecting the posterior thalamus or dorsal or ventral vicinity of thalamus or brain stem

•Patients with lesions involving the semi-oval white matter in topography consistent with sensory thalamo-cortical connections and presenting with clinical syndrome consistent with TPS

•Chief complaints of intractable hemibody pain that has remained at an average score >5 on the visual analog scale (VAS, scores ranging between 0 and 10) for 30 days, pinprick hypoesthesia over the affected hemibody (anesthesia dolorosa), severe allodynia, significant pain-related disability (Pain Disability Index or PDI score >30), failure to respond to at least one medication within each class of drugs prescribed commonly for central pain syndrome, including antidepressants, anti-seizure medications and oral narcotics.

#### Exclusion criteria

•Issues with psychiatric health, including inability to cope with implantable hardware, severe uncontrolled depression, bipolar disorder, severe obsessive compulsive disorder, suicide ideation within 12 months prior to enrollment or communication of a plan should the investigational treatment fail or imminent suicide risk (measured based on the Montgomery-Asburg Depression Rating Scale (MADRS) and the Columbia-Suicide Severity Rating Scale (C-SSRS) and the Beck Depression Inventory (BDI)

•Unstable physical health, other neurological lesions or MRI-based incidental findings unrelated to the offending lesion, women of childbearing age who are pregnant at the time of enrollment or are not using adequate contraception

•Co-morbidities including ongoing anticoagulation/anti-aggregation therapy, uncontrolled hypertension or major organ system failure

•Prior or concurrent therapies related to TPS, including previous ablative intracranial surgery for management of TPS, previous DBS therapy or simultaneous enrollment in another clinical trial for TPS

•Issues with cognitive health or ability to communicate, such as inability to provide informed consent, severe aphasia or inability to comply with the logistical requirements of the research study

Patients are being recruited from the Cleveland Clinic Neurological Institute Centers and from the Cleveland Clinic Pain Management Center. Other institutions in Northeastern Ohio and neighboring states have also been contacted about the study. These centers have access to the objectives of the study, intended population and study criteria, but patients are only enrolled and treated at the Cleveland Clinic.

### Study protocol: phases of the study

#### Phase I: screening and enrollment

Screening involves standard review of history, physical and neurological examination, review of MRI within the past year, pain questionnaires, psychiatric evaluation, pain psychological evaluation and laboratory tests. Patients meeting selection criteria are enrolled.

#### Phase II: pre-operative baseline evaluation

Phase II, or pre-operative baseline evaluation (Figure 1), involves collection of several clinical outcome measures, including extensive neurological, neuropsychological pain and cognitive and psychiatric assessments (Figure 1, Table 1). These assessments are performed before implantation, and repeated during the randomized phase, and again during the open-label follow-up phase. These evaluations are conducted by the same specialized team that routinely assesses neurologic, neuropsychological, cognitive and neuropsychiatric function in our clinical program and in our research studies in DBS. Patients also undergo functional neuroimaging (Figure 1).

**Figure 1 F1:**
[figure not shown]
**Study design.** Flowchart of the study design based on specified CONSORT clinical trial guidelines [23]. Categories defined in CONSORT guidelines are marked on the right margin of the figure. ^*^Time points when neurological, neuropsychological pain or neuropsychological cognitive evaluations (Table 1) will be conducted. During phase V, fMRI and MEG evaluations will be conducted at 2 and 5 months after randomized intervention allocation. During the open-label phase, follow-up assessments are conducted at month 9, 12, 18 and 24 for outcomes listed above and at month 12 and 24 for fMRI and MEG. TPS, thalamic pain syndrome; DBS, deep brain stimulation; fMRI: functional magnetic resonance imaging; MEG: magneto-encephalography; EuroQOL (EQ-5D), Euro Quality of Life scale.

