#### Phase III DBS implantation

All enrolled patients receive DBS implantation bilaterally in the VS/ALIC target. DBS lead implantation is completed in the same fashion as previously described by our group, but for the VS/ALIC target [18,24]. The VS/ALIC is targeted approximately at its junction with the anterior commissure and the electrodes are advanced further ventrally along the trajectory towards the VS. Once inserted, intraoperative testing with macrostimulation through the DBS lead is performed. Based on prior experience [20], we have noted that the most ventral electrode contacts elicit acute changes in mood or anxiety. At this stage, it is unknown if stimulation also produces changes in pain perception. If no effects are seen, the implanting team may consider revising the location of the lead(s). Once a location is identified, DBS leads are anchored to the skull and surgical sites are closed. The implantable pulse generator (IPG) is positioned in the infraclavicular area and connected to DBS leads under general anesthesia. Since the surgical intervention and general anesthesia may be a risk for cognitive decline, we serially assess cognitive function to note whether any patients experience negative effects on cognition related to our interventions (see Table 1).

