### Feasibility of blinding

Our current trial is a double-blinded study where neither patients nor investigators performing outcome assessments know whether DBS or sham is delivered. Maintaining a blinded study is important because of the subjective nature of reports of pain and disability. Loss of blinding may occur due to the magnitude of the therapeutic effect or any other subjective perception that indicates that active DBS or sham is delivered. Safeguards have been incorporated to prevent loss of experimental blinding; for instance, stimulation is turned to 0 V after the programming and titration in phase IV to minimize the chance of memory of stimulation affecting the patient’s perception of receiving active DBS or sham in blinded phase V. In addition, patients and blinded investigators are asked separately via questionnaire, what they believe is the status of the stimulation (active or sham). At the end of the study, we will evaluate how effective the blinding strategy was in order to guide us forward.

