Both MEG and fMRI are exploratory in this study. With fMRI, one of our goals is to evaluate resting state fMRI, comparing networks when DBS is turned on versus when it is turned off. Patients will undergo resting-state fMRI at pre-operative baseline, during the randomized blinded phase and during follow up. Thus, by comparing the DBS-on and DBS-off conditions, we will be able to assess the effects of active versus sham DBS without confounds related to placebo or study-related effects. The next goal is to correlate changes in the neural networks related to the placebo effect; we intend to do so by comparing effects of DBS-off stimulation between active, sham and pre-operative baseline phases. With MEG, we aim to harness its high temporal resolution to assess possible effects of DBS on pain anticipation. The primary hypothesis is that DBS will have a significant effect upon the affective sphere of chronic pain. Pain anticipation is one of the conditions leading to pain habituation and chronic pain. Thus, we theorize that improvements in the affective sphere will also be correlated to how cortical networks in patients with TPS modulate in pain anticipation. In order to test this concept, we have created a visual paradigm of pain anticipation that consists of a simple, three-second countdown. The type of visual paradigm encodes whether or not a painful stimulus would follow the countdown. One of the limitations related to this paradigm is that we do not have a full characterization of how healthy individuals respond to pain anticipation in this task. This can limit our understanding of how processing of pain anticipation is abnormal in individuals with TPS, and could as well limit the interpretation of effects of active DBS. In order to address these limitations, we are also evaluating a cohort of 10 healthy subjects to allow comparisons.

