#### Sample size estimation and efficacy

Since the study is designed as a randomized, sham-controlled, double-blinded study, we will also be able to evaluate whether any potential trend indicates efficacy, which would help compute effect sizes and variance in DBS versus sham phases to estimate sample sizes for adequate power in future. Our within-subject, crossover design would also yield the magnitude of placebo effect related to the surgical process itself that is an important practical issue to consider in effect-size estimates for the future.

This study was initially planned to involve a total of 34 patients. The sample size was estimated based on changes in PDI in patients with central pain syndrome in an earlier study [37]. It was determined that to detect an effect size of 0.5 (equivalent to a 7-point decrease in PDI), a total of 34 patients would need to have been included for statistical power of 80% on a two-sided test with a type I error probability of 0.05. The Food and Drug Administration of the United States has, however, determined in its review that the study should initially enroll 10 patients as part of a phase I, safety study.

Due to the small sample size of the proposed pilot phase I trial, procedures for corrections for multiple comparisons cannot be instated; the scope of the subsequent phase II trial would be better suited to include such procedures. By examining only a priori hypotheses, we aim to mitigate the probability of making type I errors. Therefore, we will compare the differences in the primary and secondary outcomes in the third month of DBS with those in the third month of sham stimulation using the paired *t*-test at α = 0.05. Despite the sample size limitation, we expect the study to be informative in estimating the magnitude of the placebo effect after DBS for pain, as well as variances in outcome that to date are unknown. These will be valuable in designing subsequent phase II and III studies.

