## Discussion and conclusions

Our protocol aims to test the safety, feasibility and preliminary efficacy of a novel, neuromodulation therapy for intractable TPS. Our approach is based on the premise that failure of traditional cerebral neuromodulation in TPS with DBS [4,5,13,16] emerges from over-reliance on modifying the percept of pain by stimulating sensory-discriminative substrates that may be unviable owing to the offending lesions. Further, since the affective component of pain experience is equally, if not more important than the perceived intensity of pain, targeting regions such as VS/ALIC may successfully modify pain experience without necessarily modifying perception of pain intensity. The level of evidence, however, supporting efficacy for DBS in chronic neuropathic pain is mainly considered class III (descriptive case series, unblinded designs) [38], attributed to poor control of confounders of therapeutic benefit of neuromodulation. While addressing our research question, we have built study design refinements to potentially inform current and future clinical DBS trials in the field.

The ethical-scientific dilemma of introducing a control arm is particularly intense in neurosurgery, given the risk of interventions to the brain. However, since DBS allows for all patients to be implanted at first and then be randomized to active stimulation or sham, studies have explored randomized controlled designs in the use of DBS, particularly in movement disorders [39-42]. Thus, to balance ethical issues (potentially effective treatment compared against control or less effective treatment) with the importance of generating rigorous empirical evidence, we have incorporated a randomized, controlled, crossover design, where both active DBS and sham groups switch to the other intervention after 3 months from their initial randomization. That therapeutic benefits may carry over from the DBS into the sham phase cannot be completely discounted. By evaluating outcomes between active DBS and sham in the third month of corresponding treatments, we expect to minimize the influence of carry over; by noting difference in outcomes between the third month of the initial treatment and the first month of the intervention after crossover, we may also be able to define an adequate time lapse for future crossover studies.

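### Blinded-phase imaging that appears to require a change of stimulation opens the month in which PDI is compared, and no safeguard for blinding is described for it

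*Protocol article*

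**What the plan says.** All references are to the protocol article.

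- **Imaging times** (Figure 1 legend): "During phase V, fMRI and MEG evaluations will be conducted at 2 and 5 months after randomized intervention allocation".
- **Imaging contrasts** (Secondary endpoints, neuroimaging paragraphs): the first goal is "comparing networks when DBS is turned on versus when it is turned off". A further goal is "comparing effects of DBS-off stimulation between active, sham and pre-operative baseline phases". On when the scans are done: "Patients will undergo resting-state fMRI at pre-operative baseline, during the randomized blinded phase and during follow up". The same paragraph calls fMRI and MEG exploratory and says that the on/off comparison avoids placebo and study-related confounding.
- **Period length** (Discussion and conclusions): "both active DBS and sham groups switch to the other intervention after 3 months from their initial randomization".
- **Efficacy comparison** (Sample size estimation and efficacy): "we will compare the differences in the primary and secondary outcomes in the third month of DBS with those in the third month of sham". The test is a paired t-test.
- **Effects of stimulation** (Phase III): prior experience is that "the most ventral electrode contacts elicit acute changes in mood or anxiety". Phase IV allows settings that affect mood and anxiety to be chosen for chronic use when the affective report of pain does not respond. Table 2 lists symptom rebound on cessation of stimulation as a risk.
- **Blinding** (Feasibility of blinding): "Maintaining a blinded study is important because of the subjective nature of reports of pain and disability". The measures described there, in Phase V and in the Discussion are a generator that always reads as on, about a month without stimulation before randomization, blinded outcome assessors kept apart from programmers, and questionnaires on believed allocation.

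**The concern.** Each of these statements is reasonable alone. The difficulty is how they combine. An exploratory imaging study that seems to need stimulation taken off, and then restored, within blinded treatment is placed at the opening of the month in which the self-reported primary outcome is compared.

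A patient who notices the change could infer the allocation shortly before reporting PDI and VAS. That would work against the month without stimulation that the plan inserts to let the memory of stimulation fade. The section on Safety and feasibility already accepts the same mechanism at crossover: loss of an effective stimulation could be noticed and could compromise blinding. It does not extend that reasoning to the imaging visits. The statement that the on/off comparison is free of placebo confounding would also fail for a within-session contrast if the patient can feel the switch.

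**Working it through.** **1. Is a change of stimulation implied?** Two readings of the imaging paragraph are possible.

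- *On means the active-period scan and off means the sham-period scan.* The first goal can then be met without any switching. The second goal cannot: it compares DBS-off across the active, sham and baseline phases, and on this reading there is no off scan in the active phase.
- *An off scan is taken within the active phase.* The second goal can then be met, but stimulation must be changed during blinded treatment.

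So either stimulation changes at the active-period visit, or the second goal has no data for one of its three phases. Sham is 0 V (Phase V), so an off scan in the sham period needs no change, and no on scan in that period is stated.

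**2. Calendar.** Periods run from month 0 to 3 and from month 3 to 6. The third month of each is month 2 to 3 and month 5 to 6. Imaging is at months 2 and 5. The gap from imaging to PDI is 2 − 2 = 0 to 3 − 2 = 1 month in period 1, and 5 − 5 = 0 to 6 − 5 = 1 month in period 2.

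**3. Which outcomes follow the implied change?** Assume a change in the active period only.

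| Sequence | Implied change | Period-1 PDI (months 2–3) | Period-2 PDI (months 5–6) |
|---|---|---|---|
| Active first | month 2 | 0–1 month later | 3–4 months later |
| Sham first | month 5 | already collected | 0–1 month later |

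Three of the four sequence-by-period outcomes come after a change of stimulation. The active-first, period-2 outcome is included because a patient who learns one period's allocation in a two-period crossover knows the other.

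**4. Size.** The plan's own figure reproduces: an effect size of 0.5 for 7 PDI points implies an SD of 7/0.5 = 14, and a paired t-test at two-sided 0.05 has power 0.808 with 34 patients and 0.795 with 33. That figure is not in dispute. With the 10 patients now planned, power at the same effect is 0.29.

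The document gives neither the share of patients who would notice the change nor the effect of noticing on PDI. For illustration only, let u be the share who infer their allocation and b the resulting shift in their DBS-minus-sham PDI difference, with no true effect, SD of the paired difference 14 and n = 10. Bias = u × b.

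| u | b | Bias (PDI points) | Chance of p < 0.05 |
|---|---|---|---|
| 0.25 | 3 | 0.75 | 0.053 |
| 0.25 | 7 | 1.75 | 0.065 |
| 0.5 | 3 | 1.5 | 0.061 |
| 0.5 | 7 | 3.5 | 0.109 |
| 1 | 3 | 3 | 0.093 |
| 1 | 7 | 7 | 0.293 |

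The result runs from negligible to a bias as large as the planning effect, depending wholly on the assumed u and b.

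**The case against.** A reader might infer more than the text supports, and on these points the objection is right.

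- *That switching is stated.* It is not. It is a strong inference from the second imaging goal. The first goal alone can be read as a comparison of active with sham periods.
- *That patients are switched in both periods, so that feeling nothing reveals sham.* Nothing states that stimulation is turned on at a sham-period visit.
- *That imaging falls a full month before PDI.* The plan says only the third month, so one month is the upper end of the gap.
- *That patients will be unblinded.* The mood and anxiety observation appears in the account of implantation and intraoperative testing. Nothing shows that a brief interruption of chronic stimulation during a scan is felt.

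It can also be said that a journal article leaves scan order and masking to the full protocol, that guesses are recorded and the DSMB reviews threats to blinding, and that this is a 10-patient phase I pilot looking for a trend. The absence of an imaging manual is indeed no fault. But the article itself fixes the imaging months, the contrasts and the outcome month, and the problem lies in their combination. Recording guesses detects loss of blinding but does not prevent it. A pilot meant to supply the placebo effect and variance for later trials still needs its blinding intact.

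Finally, re-ordering is only a partial remedy in a crossover. That stands and is counted as a cost of the fix.

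**Conclusion.** The point holds as a credible risk. The imaging goals imply a change of stimulation at least at the active-period visit, that visit opens the month of the PDI comparison (0 to 1 month before it), and none of the safeguards described addresses it. Plausibility comes from the article's own statements on acute mood or anxiety effects, on settings chosen for such effects, on rebound and on worsening after active stimulation.

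The conclusion rests on two inferences: that the second imaging goal is meant literally, and that some patients would notice. The size of any bias cannot be derived from the document; the range of 0.75 to 7 PDI points rests on assumed inputs. The document supports neither certain unblinding nor switching in the sham period. The matter deserves a change because the change is cheap and the article reports that the trial is still enrolling.

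**What to change.** 1. State whether stimulation is changed at the blinded-phase imaging visits, in which periods, and how this is masked, so that the Figure 1 legend, the imaging goals and the blinding section agree.
2. In each blinded period, complete PDI, VAS and the treatment-guess questionnaire in the third month before any imaging session that changes stimulation. Then image before crossover (period 1) or before the open-label phase (period 2).
3. Repeat the guess questionnaire after imaging, so that any loss of blinding due to the session can be seen.
4. Use the blinded between-period contrast, active versus sham, as the placebo-controlled imaging comparison. Drop the claim that a within-session on/off contrast is free of placebo confounding.

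**Cost.** The imaging visits move and one short questionnaire is repeated; no other procedure is added. The month-3 and month-6 visits become fuller. Imaging just before crossover would also sit next to the first-month-after-crossover comparison that the Discussion plans for studying carry-over.

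**What it protects.** Every period-1 outcome is protected. If stimulation changes only in the active period, the sham-first group's period-2 outcome is protected too, because its active-period scan then follows PDI. The active-first group's period-2 outcome remains exposed: imaging at month 3 precedes it by 5 − 3 = 2 to 6 − 3 = 3 months, and knowledge of allocation need not fade in that time. On this reading the exposed outcomes fall from three of four to one of four. If sham-period sessions also involve a change, the sham-first group's period-2 outcome is exposed as well.
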